#### Secondary outcomes

Secondary outcome measures (including the primary outcome measures at the other follow-up time-points) will be analysed using generalised linear models, with link function appropriate to the type of data. Models will be adjusted in the same way as the primary outcome, using the baseline value of the outcome measure (where applicable). Time to events (transition to first episode (hypo)mania and recovery from BAR symptoms) will be analysed using a Cox proportional hazards model, adjusted for stratification factors. Tests will use a 5% significance level and two-sided 95% CIs will be presented.

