#### Inclusion criteria

i.16–25 years old,ii.Help seeking,iii.Able to provide written, informed consent, andiv.Meets criteria for at least one BAR group within the last 12-months (See Table 2).

**Table 2 Tab2:** Bipolar At Risk (BAR) groups (Adapted from Bechdolf [14] with modified group classifications)

BAR group name	Criteria as assessed by the Structured Clinical Interview for DSM-5 Research Version (SCID-5-RV)	Duration of symptoms
1. Subthreshold mania	Abnormally and persistently elevated, expansive or irritable mood and at least two criteria from the symptom list (three if mood is irritable): Inflated self-esteem/grandiosity; Decreased need for sleep; More talkative than usual or pressure to keep talking; Flight of ideas or racing thoughts; Distractibility; Increased goal-directed activity or psychomotor agitation; excessive involvement in activities that have a high potential for painful consequences	At least two consecutive days but < 7
2. Depression + cyclothymic features	Depressed mood or loss of interest/pleasure for at least one week and at least two criteria from the symptom list: Significant weight loss; Insomnia or hypersomnia nearly every day; Psychomotor retardation or agitation; Fatigue or loss of energy; Feelings of worthlessness or excessive/inappropriate guilt; Diminished ability to think or concentrate; Recurrent thoughts of death or suicidal ideation *Plus* *S*ubthreshold mania symptoms as described in group 1 (but see “Duration of symptoms”)	Depression: at least one week Subthreshold mania symptoms: four hours within 24-h period, on at least four cumulative, lifetime days
3. Depression + genetic risk	Depression symptoms as described in group 2 *Plus* First-degree relative with BD	Depression: at least one week

^*^When a participant meets more than one BAR group at baseline, the BAR group for randomisation input will be decided using a hierarchical rule, with BAR Group 1 entered when met, BAR Group 2 entered when met on own or in combination with BAR Group 3, and BAR Group 3 only entered when met alone

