#### Exclusion criteria

i.History of a treated/untreated manic episode or psychosis of 1-week duration or longer,ii.Treatment with a mood stabiliser for longer than 6 weeks or antipsychotic for 3 weeks (that evidence exclusion on point above or at the time of the assessment whereby at-risk status cannot be confirmed),iii.Organic brain disorder,iv.Inability to complete assessments due to language barriers,v.Inpatient/acute psychiatric care needed, or primary substance abuse/dependency.

To ensure the study results are readily translatable within the current NHS, recruitment will involve outreach to a variety of services including children and young people’s mental health services, early intervention and detection teams (EDIT/EIT), Community Mental Health Teams (CMHT), Improving Access to Psychological Therapies (IAPT), primary care psychology services, GPs, schools, university health services, other youth services and the voluntary sector. Teams will be provided with study materials and be asked to identify potentially eligible individuals to refer to the research team. Referrers will discuss the study and obtain consent-to-contact for researchers who will then provide the individual with information to enable them to provide informed consent. Potential participants will be screened for potential eligibility before informed consent is taken. After written informed consent is obtained, BAR status will be established using the SCID-5-RV [39] and eligibility confirmed with the chief investigator or their delegate. Participants will be informed that they can withdraw from the trial at any point, without giving a reason and without it affecting their care.

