#### Data analyses

Quantitative analyses will be undertaken using the principles of intention-to-treat, where participants are analysed according to the group to which they were randomised, regardless of what treatment they received. Analysis will be undertaken using Stata v18.0 (or later) [45], using two-sides tests at a 2.5% significance level, with 97.5% confidence intervals provided, unless otherwise stated. All quantitative analyses will be pre-planned and included in a Statistical Analysis Plan which will be finalised and approved by the TSC prior to database lock and analysis.

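### Time to first (hypo)mania may include participants who had already had a hypomanic episode before randomisation

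*Protocol article*

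**What the plan says.** **The outcome.** The Secondary outcomes paragraph of the data analysis section of the protocol article plans two time-to-event analyses: "Time to events (transition to first episode (hypo)mania and recovery from BAR symptoms) will be analysed using a Cox proportional hazards model". The model is adjusted for the stratification factors, which are site and BAR group. No at-risk subset is named. On significance: "Tests will use a 5% significance level and two-sided 95% CIs will be presented". The Data analyses section sets the general rule: "Quantitative analyses will be undertaken using the principles of intention-to-treat".

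**Entry.** The inclusion criteria require only this of BAR status: "Meets criteria for at least one BAR group within the last 12-months". In Table 2, Group 1 needs abnormal mood with "at least two criteria from the symptom list (three if mood is irritable"), for a duration of "At least two consecutive days but < 7". Group 2 needs depression plus short spells of the same manic symptoms: "four hours within 24-h period, on at least four cumulative, lifetime days".

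**Exclusion.** The only exclusion that refers to earlier episodes is: "History of a treated/untreated manic episode or psychosis of 1-week duration or longer". Hypomania is not mentioned.

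**Expected baseline state.** The section on sample size and power expects entrants in the upper subthreshold range of the LIFE rating (3–4). It also says that people rated 5–6 would be ineligible, but no such rule is among the listed criteria.

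**The concern.** A time-to-first-event analysis needs everyone in the risk set to be free of the event at time zero. Here the event boundary is set at hypomania, while the exclusion boundary is set at mania of a week or more. Between the two lies a range of episodes that the entry rules permit, and that Group 1 uses as its qualifying feature. For someone who enters on such an episode, a later one of the same kind is a recurrence. As written, the plan would count it as a first transition.

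A lower likelihood of transition to bipolar disorder is one of the efficacy hypotheses in the abstract. If the event count mixes first episodes with recurrences, the hazard ratio does not cleanly answer that question, and readers cannot tell how much of it concerns prevention.

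**Working it through.** **1. The plan's own figures.** The article gives no event rate, hazard ratio or power for either time-to-event outcome, so there is no figure to correct. The stated sample size concerns LIFE depression. With SD 1.3, baseline correlation 0.4, difference 0.5, two-sided 2.5% and 90% power, n per arm = 2 × (2.241 + 1.282)² × 1.3² × (1 − 0.4²) / 0.5² = 141, or 282 in total against 286 stated. It is reproduced closely and does not depend on the present point.

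**2. The boundaries side by side.**
- Excluded: mania or psychosis of a week or longer.
- Admitted by Group 1: elevated or irritable mood for 2, 3, 4, 5 or 6 days. The symptom count has a floor of two (three if irritable) and no ceiling, so all seven listed symptoms may be present.
- Counted as the event: a first episode of (hypo)mania.

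**3. Overlap.** The article states no duration threshold for hypomania, so it is taken here as an unknown.

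| Assumed threshold (days) | Group 1 durations that are eligible and already long enough to be an episode |
|---|---|
| 2 | 2–6 |
| 3 | 3–6 |
| 4 | 4–6 |
| 5 | 5–6 |
| 6 | 6 |
| 7 or more | none |

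Any threshold below 7 days leaves an overlap. The Group 1 label of subthreshold mania does not close it, because no written criterion caps the symptoms.

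**4. Possible dilution (all inputs assumed).** Let f be the share of entrants with earlier hypomania. Take a one-year risk of 10% v 5% in the others (ratio 0.50), and 30% v r in those with earlier hypomania. Observed risk ratio = [(1 − f) × 0.05 + f × r] / [(1 − f) × 0.10 + f × 0.30].

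| f | r = 0.15 (same benefit) | r = 0.225 (half the reduction) | r = 0.30 (no benefit) |
|---|---|---|---|
| 10% | 0.060/0.120 = 0.50 | 0.0675/0.120 = 0.56 | 0.075/0.120 = 0.63 |
| 20% | 0.070/0.140 = 0.50 | 0.085/0.140 = 0.61 | 0.100/0.140 = 0.71 |
| 30% | 0.080/0.160 = 0.50 | 0.1025/0.160 = 0.64 | 0.125/0.160 = 0.78 |

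These are crude risk ratios, not adjusted hazard ratios. The result depends on the benefit in those with earlier hypomania as much as on f.

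**5. Price of restricting the risk set (assumed hazard ratio 0.5).** With D events, power = Φ(√D × ln 2 / 2 − 1.96). Attrition is ignored.

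| Share removed | N | Power, 20% with an event | Power, 10% with an event |
|---|---|---|---|
| 0 | 338 | 81% | 52% |
| 10% | 304 | 77% | 48% |
| 20% | 270 | 72% | 44% |
| 30% | 237 | 67% | 39% |

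**The case against.** **Event definitions belong in the analysis plan.** The article is condensed, the statistical analysis plan is not shown, and it may define the event and the risk set. This stands as far as missing detail goes, and it limits the point to what may happen. It does not remove the mismatch, because both boundaries are fixed in the article and they differ.

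**The overlap rests on a threshold that the article does not give.** This stands, which is why it is stated as an assumption with a range.

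**BAR group is a covariate.** Under the footnote to Table 2, anyone meeting Group 1 is coded as Group 1, so the model partly separates people with recent short elevated spells. Only partly: Group 1 can hold people above and below a hypomania threshold, and an episode more than 12 months old can sit in another group.

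**The sample size section expects subthreshold ratings.** That is an expectation about symptom severity, in a paragraph deriving the depression sample size. It says nothing about past hypomanic episodes.

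**Stronger readings that the documents do not support.** A reader might infer that the transition analysis does contain people who have had the event. The text permits it and gives no count. A reader might also take 0.63 to 0.78 as the expected attenuation, but those values assume no benefit in people with earlier hypomania. Finally, since BAR criteria need only have been met in the past 12 months, a reader might infer that people already well at entry will be counted as early recoveries. Recovery is not defined in the article, the unseen plan may settle it, and current symptoms are expected, so that does not follow.

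**Conclusion.** The point holds for transition, as a possibility created by the text. The entry rules and the event definition overlap under any hypomania threshold from 2 to 6 days, and no restriction of the risk set is stated. The number of participants affected cannot be derived from the article.

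Because earlier hypomania is fixed before randomisation, the arms stay comparable and no bias between arms follows. What suffers is the meaning of the estimate, with dilution that ranges from none to substantial depending on the treatment effect in people with earlier hypomania. The outcome is secondary, and the co-primary analyses are untouched. It still merits a change, because transition carries one of the trial's main hypotheses. For recovery, only a clarification is warranted.

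**What to change.** Reconcile Table 2, the exclusion criteria, the statement on ratings of 5–6 in the sample size section, and the time-to-event sentence. Then, in the statistical analysis plan, before database lock:

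1. State the definition of hypomania and of mania used for the transition event.
2. From the baseline SCID-5-RV, flag participants whose qualifying or past episode already meets that hypomania definition, and report the number by arm.
3. Analyse time to first manic episode in all randomised participants, since entry excludes earlier mania of a week or longer.
4. Analyse time to first (hypo)mania in participants without the flag, and show the all-participant analysis alongside it.
5. For recovery, state how participants without current BAR symptoms at randomisation are handled.

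The work is a few sentences and one derived variable. The flag should be obtainable from the baseline interview, provided that it recorded episode length and symptoms. Restricting on a pre-randomisation variable keeps the randomised comparison. The real cost is fewer participants and events in the restricted set, with the loss of power shown in the working. That is a reason to keep the all-participant result in view.

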### Randomisation and masking

Following informed consent and entry to the trial, participants will be randomly allocated to one of two trial arms. Randomisation will be independent and concealed, using permuted stratified blocks (by site (5-levels) and BAR group (3-levels)) via a web-based system at York Trials Unit (YTU). Stata v18.0 [45] was used to generate the allocation schedules. Researchers will enter participant’s details into the randomisation system and the outcome communicated to the chief investigator, trial management and administrators. Participants, their GP, and referrers will be informed about the allocation via letter.

Assessor’s will be masked to treatment condition. Masking will be maintained using various measures including separate offices for therapists and research assistants, reminders about masking, protocols for message taking, and data security using passwords and encryption. Letters to participants and clinicians will contain a standardised statement about the need to maintain the masking process. Unmasking will be recorded, and where possible an independent assessor with whom the masking has not been broken will complete follow-ups.

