Assuming a SD of 1.3 [73], a conservative correlation of 0.4 between baseline and 27-weeks [76] a 2.5% two-sided significance level, and a between group mean difference of 0.5 points in mean 4-week PSR for LIFE [50] depression at 27-weeks, we would require 286 participants with outcome data to achieve 90% power. Inflating the sample size to allow for a conservative 15% attrition (13% in the feasibility trial) [74] requires a target to randomise of 338 participants (approximately 68 per site). This sample size would also provide 98.5% power to detect a more conservative MCID on LIFE [50] PSR for mania, target effect of 0.25 points, estimated within-group SD = 0.5 points [73]. In each case, power will be increased due to the (multiple) correlation between outcome and the full set of explanatory variables adjusted for in the model. A random therapist effect is not accounted for in our sample size calculation as the effect on the BDI-II in our feasibility trial was 0, although the confidence interval was wide. This will be explored within a sensitivity analyses.

For the qualitative component we will recruit two groups of 15–25 people each for individual interviews. One group will be participants from the intervention arm of the trial across all five sites and one group will comprise key stakeholders including health professionals, service providers and commissioners. To build upon the acceptability work in the original BART trial, we will seek a more diverse and inclusive sample (e.g. ethnicity, socioeconomic status, gender) and level of engagement in therapy, including non-responders. The stakeholder groups will include health professionals involved in delivery of CBT_BAR_ and other interventions and services for this population, and referrers (and potential referrers) to the trial from a range of services and across geographical area.

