#### Co-primary outcomes

The primary analyses for each of the co-primary outcomes (mean 4-week PSR for LIFE depression score and for LIFE mania score at 27-week follow-up) will use analysis of covariance, with adjustment for the stratification factors (site and BAR group), the baseline PSRs for depression and mania and prior CBT (yes/no). For each outcome, if less than 15% of participants are excluded from the analysis due to missing data, and the differential amount of missing data between the trial arms is less than 10% then complete case analysis will be used. Otherwise, multiple imputation by chained equations (MICE) [77] will be used, assuming that the data are ‘missing at random’. The opposite method will be used as sensitivity analysis. To explore whether BAR group and prior CBT could act as potential moderators of the co-primary outcomes, the analysis will be repeated with the inclusion of interaction term, for each of these variables with treatment arm, separately.

Casual inference methods for mediation [78] will be used to estimate the indirect effect of CBT_BAR_ on each of LIFE mania and LIFE depression scores via the HAPPI total score at the preceding time-point (e.g. 17-week HAPPI for 27-week LIFE scores). A more complex causal model incorporating Behaviours Checklist and Internal State Scale will be investigated using structural equation modelling. As a post-randomisation effect modifier, the impact of the number of CBT_BAR_ sessions attended will be assessed using principal stratification methods; other measures of intervention receipt, including antidepressant medication, will be considered in separate analyses.

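### The Cox model for time to recovery omits baseline symptom severity, which the trial already collects; adding it is a small, low-priority gain in efficiency

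*Protocol article*

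**What the plan says.** Under Secondary outcomes, the protocol article sets the covariates by type of model. For the generalised linear models the rule is "Models will be adjusted in the same way as the primary outcome, using the baseline value of the outcome measure (where applicable". For time to transition and time to recovery the rule is that they "will be analysed using a Cox proportional hazards model, adjusted for stratification factors". Under Randomisation and masking, the stratification factors are site (five levels) and BAR group (three levels).

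Under Co-primary outcomes, the analysis of covariance is planned "with adjustment for the stratification factors (site and BAR group), the baseline PSRs for depression and mania and prior CBT (yes/no". Under Sensitivity analysis, the longitudinal mixed model also takes both baseline PSRs alongside the stratification factors.

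For the secondary outcomes, "Tests will use a 5% significance level and two-sided 95% CIs will be presented". The article states no event count, hazard ratio or power for either time-to-event outcome.

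**The concern.** Recovery from BAR symptoms is the secondary outcome for which starting severity is most plausibly prognostic. Yet the Cox models are the only treatment-effect models in the analysis section whose stated covariates include neither the baseline PSRs nor a baseline value of the outcome. Randomisation is not stratified by severity, so the design does not balance it directly.

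Two things follow if severity does predict recovery. First, leaving a prognostic covariate out of a Cox model moves the estimated treatment hazard ratio towards 1 and lowers power, even when the arms are balanced. Second, a chance difference in severity between the arms is not adjusted for in the recovery hazard ratio, although it is in the 27-week PSR comparison. The article itself values this kind of adjustment: its sample size relies on the correlation with baseline, and it expects the full covariate set to raise power further.

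**Working it through.** **1. The plan's own figure.** The only powered comparisons are the co-primary ones. Inputs from Sample size and power calculations: SD 1.3, baseline correlation 0.4, difference 0.5, two-sided alpha 2.5%, power 90%. Equal allocation is assumed.

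- Adjusted SD = 1.3 × √(1 − 0.4²) = 1.191.
- n per arm = 2 × (2.241 + 1.282)² × 1.191² / 0.5² = 141, so 282 in total against 286 stated. The t-based power at 143 per arm is 90.2%.
- 286 / 0.85 = 336.5, which gives 338 as an even number.
- Without the baseline adjustment the same formula gives 336 analysed.

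The stated figure is reproduced. It also shows that the design counts on baseline PSR being informative.

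**2. How prognostic might severity be for recovery?** The article does not say. The nearest figure is the assumed correlation of 0.4 between baseline and 27-week depression PSR. As an illustration, suppose that recovery means falling below a cut-off c on a normal score correlated 0.4 with standardised baseline severity x. Then P(recover | x) = Φ((c − 0.4x)/√0.84). Half the difference in ln(−ln(1 − P)) between x = −1 and x = +1 approximates the size of the log hazard ratio per SD.

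- 50% recovering (c = 0): P = 0.669 and 0.331, giving 0.100 and −0.911, so (0.100 + 0.911)/2 ≈ 0.51.
- 60% recovering: about 0.46. 30% recovering: about 0.62.

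A value near 0.5 is therefore compatible with the plan's correlation. It is an indication only.

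**3. Power of the recovery model without and with severity.** Exponential event times, two-sided 5% test, one standard normal severity covariate. All event rates and hazard ratios are assumptions.

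- Setting A: 338 randomised, 15% lost uniformly over 52 weeks, 40% recovery in TAU, HR 1.6, about 155 events, site and BAR group in both models, 1,000 runs.
- Setting B: 286 patients, 50% recovery in TAU, HR 1.5, no site or BAR terms, 1,000 runs.

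| Log HR per SD | A: without → with | B: without → with |
|---|---|---|
| 0 | not run | 73% → 74% |
| 0.3 | 81% → 81% | 72% → 74% |
| 0.5 | 79% → 83% | 65% → 73% |
| 0.7 | 72% → 84% | not run |
| 0.8 | not run | 56% → 72% |

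A smaller check (338 randomised, 15% dropout, 300 runs, no site or BAR terms, log HR 0.5 per SD) gave 78% → 84% at HR 1.6 with 40% recovery, and 71% → 78% at HR 1.5 with 50% recovery. With 1,000 runs the Monte Carlo standard error of a power near 80% is √(0.8 × 0.2/1000) = 1.3 points; with 300 runs it is 2.3 points.

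The estimated hazard ratio without severity fell from 1.59 to 1.56 to 1.52 in setting A (log HR 0.3, 0.5, 0.7), against about 1.62 with it. In setting B it fell to 1.40 at 0.8, against 1.51 with it. With a true HR of 1.0, rejection was about 5% in both models in setting A. In setting B it ranged from about 3% to 6.5% over event proportions of 10% and 50%, with or without the covariate.

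**4. Chance imbalance.** The SE of the difference in mean standardised severity between arms is 2/√338 = 0.109. At 0.5 per SD, an imbalance of one SE moves the log hazard ratio by 0.5 × 0.109 = 0.054. With about 155 events the SE of the log hazard ratio is near 2/√155 = 0.161, so the shift is about one third of an SE.

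**5. Transition.** With an assumed 15% transition in TAU and HR 0.45 (about 36 to 42 events), adding severity changed power by about −1 to +4 points. Arm, site and BAR group already use 1 + 4 + 2 = 7 parameters, and three more make 10. That is about 4 events per parameter for transition, against about 15 for recovery (155/10).

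**The case against.** The strongest reply is that nothing here is wrong. A reader might infer that the Secondary outcomes section contradicts itself by giving two adjustment rules. It does not: one rule covers the generalised linear models and the other the Cox models, and a time-to-event outcome has no baseline value of its own. A reader might also infer that the Cox result would be biased or its test invalid. That is not supported either. Adjusting for the randomisation strata is a sound prespecified analysis, type I error is held, and chance imbalance is part of the sampling error that the confidence interval already covers. Part of the movement of the hazard ratio towards 1 is non-collapsibility: the two models estimate different quantities. All of this stands.

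It is also fair that the documents do not show severity to be strongly prognostic. The 0.4 is an assumed correlation for a different outcome, the article does not define recovery, and the eligible PSR range is expected to be narrow (3 to 4), which may weaken the covariate. So the loss of power is conditional and may be close to nothing. If 0.4 applies to this trial's sample, however, it already reflects that narrow range.

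Finally, a condensed article need not give a reason for a covariate set, and its absence is not held against the plan. But the set itself is stated, so the suggestion concerns a stated choice.

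**Conclusion.** The point holds as an efficiency improvement to one secondary analysis. As specified, the time-to-recovery model is valid but leaves out a covariate that the trial collects and uses in its co-primary and longitudinal models. The cost in power is about 0 points if severity is weakly prognostic, 4 to 8 points at a log hazard ratio of 0.5 per SD, and up to about 16 points at 0.8 per SD. These figures rest on assumed recovery of 40% to 50% in TAU, hazard ratios of 1.5 to 1.6, and a single severity score standing in for the two PSRs. The direction was consistent across the settings once severity was at least moderately prognostic. The case does not extend to transition, where the gain was negligible and events are likely to be few. Low priority: the co-primary analyses and the sample size are unaffected.

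**What to change.** In the statistical analysis plan, before database lock, prespecify that the Cox model for time to recovery from BAR symptoms is adjusted for site, BAR group, baseline depression PSR, baseline mania PSR and prior CBT, as in the primary analysis. Keep site and BAR group only for time to transition, and say that the expected number of events is the reason for the shorter set.

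The cost is a sentence or two and no new data, because the co-primary analysis already needs these covariates. The recovery model gains three parameters, and its hazard ratio becomes conditional on baseline severity, which the report should state.
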